#### Sample size consideration

2.2.6

According to previous research (31), the Cobb angle was 10.87 ± 3.60°in EG after treatment, compared to 14.97 ± 5.01°in CG. Using the PASS 2021 software for calculation, with a sample size ratio set at 1:1, *α* = 0.05 (two-sided test), and a statistical power (1−*β*) of 0.90, while controlling the attrition rate within 15%, it is determined that 30 patients need to be recruited for each group. Therefore, this study will require the inclusion of a total of 60 patients. In addition, we will recruit 15 healthy individuals of the same age. They will compare with patients at baseline to evaluate biomechanical changes of AIS.

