#### Primary outcome measure

2.4.1

All AIS patients will require the standing frontal radiograph. The Cobb angles will be measured by two blinded and independent radiologists before and after the treatment.

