#### Data analysis

2.5.2

All statistical analysis will be performed by an independent statistician (blinded to group allocation) using SPSS 27.0. A *p*-value of <0.05 will be considered statistically significant. Continuous data will be summarized as mean ± standard deviation (M ± SD) or median with interquartile range. Categorical variables will be presented as frequencies or percentages.

This study will employ an intention-to-treat analysis, including all participants who were randomized and received at least one intervention session. Outcomes will be analyzed using two-sample *t*-tests or paired *t*-tests. If normality assumptions cannot be met, non-parametric tests will be used. For categorical variables, chi-square (χ^2^) tests will be performed. Inter-rater reliability will be assessed using the intraclass correlation coefficient. For case data with missing values, multiple imputation will be used to address the gaps.

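### The primary Cobb test may switch to a rank test on non-normality, a branch with no usual estimate to pool over the planned multiple imputations and no link to the 4.10° mean difference used for sizing

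*Protocol article*

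**What the plan says.** The primary outcome is the Cobb angle (section 2.4.1): "The Cobb angles will be measured by two blinded and independent radiologists before and after the treatment".

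Section 2.5.2 gives one rule for all outcomes, and nothing elsewhere exempts the Cobb angle or names a single test for it:

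- "Outcomes will be analyzed using two-sample *t*-tests or paired *t*-tests".
- "If normality assumptions cannot be met, non-parametric tests will be used".
- "For case data with missing values, multiple imputation will be used to address the gaps".

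Section 2.2.6 sizes the trial on a difference in means: "the Cobb angle was 10.87 ± 3.60°in EG after treatment, compared to 14.97 ± 5.01°in CG". It uses two-sided α = 0.05, power 0.90 and attrition of at most 15%, and arrives at 30 per group.

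**The concern.** Each rule is conventional alone. Together, on the primary outcome, they leave a gap. Multiple imputation produces several completed data sets, and Rubin's rules combine an estimate and its standard error from each. The t-test branch supplies both. The rank branch in its usual form supplies a test statistic and a p-value per data set, and the article gives no way to turn these into one result.

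The rank branch also changes the question. The trial was sized to detect a difference in mean Cobb angle in degrees, but a rank test does not estimate that difference. Which quantity the trial reports as its primary result would then depend on the shape of the data.

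**Working it through.** **1. The plan's own figure.** Inputs are from section 2.2.6.

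- Difference: 14.97 − 10.87 = 4.10°.
- Common SD: √[(3.60² + 5.01²)/2] = √[(12.96 + 25.10)/2] = √19.03 = 4.36°.
- Normal approximation: n = 2 × (1.960 + 1.282)² × 19.03 / 4.10² = 23.8, so 24 per group. With attrition, 24/0.85 = 28.2, so 29.
- Noncentral t, equal-variance or Welch: 25 per group (power 0.901 to 0.902). With attrition, 25/0.85 = 29.4, so 30.

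The stated 30 per group reproduces, and it rests on a comparison of means.

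**2. Is missing Cobb data expected?** At the 15% ceiling, 0.15 × 30 = 4.5, so 4 to 5 post-treatment values per arm.

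**3. What can be pooled.** With m imputations, Rubin's rules take estimates Qj and variances Uj. They return the mean of the Qj with total variance Ū + (1 + 1/m)B, where B is the between-imputation variance. A mean difference fits this form. A Mann-Whitney p-value per data set does not.

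**4. How often the gap would appear.** Simulations used the protocol's post-treatment means and SDs with 30 per arm. Normality was judged by Shapiro-Wilk at 0.05 in each arm. That criterion, the distribution shapes and the number of imputations are assumptions; the article states none of them.

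*One check on observed data* (4 of 30 missing per arm, 20 imputations). With log-normal data the rank test was selected in 55% of trials. Rank-test significance was mixed across the imputed data sets in 11%.

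*A check in every imputed data set.* Share of trials in which the data sets called for different tests (imputation by normal regression on baseline within arm, baseline-to-post correlation 0.7, 800 trials per cell):

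| Data | Missing | 5 imputations | 20 imputations |
|---|---|---|---|
| Normal | 5% | 14% | 23% |
| Normal | 15% | 18% | 32% |
| Log-normal | 5% | 27% | 39% |
| Log-normal | 15% | 36% | 56% |

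A separate run with 4 of 30 missing per arm and 20 imputations gave 38% (normal) and 54% (log-normal).

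**5. Does the choice of test matter for error rates?**

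- Disagreement on p<0.05 between t-test and rank test, 25 per arm, 4,000 trials: about 4% for normal and for log-normal data.
- Power, t-test against switching rule: 0.902 and 0.902 (normal); 0.914 and 0.920 (log-normal).
- Type I error on skewed data, 25 to 30 per arm: 0.042 to 0.046 (Welch) against 0.045 to 0.049 (switching) in one set of runs; 0.050 to 0.054 (t-test) against 0.055 to 0.057 in another. With 6,000 trials the Monte Carlo error is about 0.003.

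**6. Effect of the fix on sample size.** None: the comparison of means is the one already sized. For contrast, if the rank test governed under normal data (assumed relative efficiency 3/π), 24/(3/π) = 25.1, so 26 per group, and 26/0.85 = 30.6, so 31.

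**The case against.** The best defence is that this is a condensed article. Which data are checked for normality, how many imputations are run and how results are pooled commonly belong in an analysis plan that is not shown. That is fair, and the absence of those details is not the point here. What the article does state is a rule that lets the primary test depend on the data, and one of its branches does not sit with the stated missing-data method. A later plan would have to override that rule or add an unusual pooling step.

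Three stronger readings are tempting, and the document does not support them.

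- *The imputed data sets will call for different tests.* This needs a normality check in each data set. The article prescribes no such check, no formal test and no cut-off. One check on observed data selects one test. The split percentages apply only under the per-data-set reading, and many of the splits are lopsided: in one run with 20 imputations, about 20 of 30 percentage points (normal) and 33 of 57 (log-normal) were 80:20 or more uneven.
- *The two rules cannot be combined at all.* The Mann-Whitney statistic divided by n1 × n2 estimates the probability of superiority. It has a standard error and can be pooled. Pooling is unspecified and less usual, but not impossible. The result would still not be in degrees.
- *The switch inflates false positives or costs power.* The figures in step 5 of the working show no material effect.

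Two safeguards also count. The statistician is blinded to allocation (sections 2.2.7, 2.5.2 and 2.6), which limits a choice made to favour one arm, although it does not define the estimate. Section 2.6 provides for contacting non-completers to complete assessments, so missingness may fall below 15%.

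**Conclusion.** The point holds in limited form. As written, section 2.5.2 lets the primary Cobb analysis move to a rank test. With imputed values, that branch has no usual pooled estimate, and it abandons the mean difference on which the trial was sized. This does not depend on simulation. How often it would occur does: under an assumed Shapiro-Wilk check on observed data it was 55% of trials with log-normal values, and it would be less of an issue if post-treatment Cobb angles are close to normal or few are missing.

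The consequence is an undefined primary estimate and p-value when the branch is triggered. It is not a material error-rate problem, given about 4% disagreement between the tests at protocol values and nearly equal type I error and power. Severity is minor to moderate.

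**What to change.** In section 2.5.2, name one primary Cobb analysis that applies whatever the normality check shows:

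- Estimate the between-arm difference in mean post-treatment Cobb angle, preferably adjusted for baseline Cobb (already collected), with robust or unequal-variance standard errors and a 95% CI in degrees. Naming the post-treatment value and the between-arm contrast also settles the open choice between two-sample and paired tests for this outcome.
- Fit it in each imputed data set and pool by Rubin's rules, with arm and baseline Cobb in the imputation model.
- Remove the normality-triggered switch for the primary outcome. Keep the rank test as a labelled sensitivity analysis on observed data.

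The cost is a sentence or two, best settled before unblinding. No extra data, staff or patients are needed, and the sample size stays at 30 per group.

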The lower limbs, pelvis and spine are interconnected. Existing studies have widely reported that AIS patients typically exhibit biomechanical abnormalities in both the spine and lower limbs, such as asymmetric muscle activation, temperature differences in muscle activity, gait abnormalities and abnormal plantar pressure distribution, which further compromise spinal stability by disrupting the biomechanical balance between spine and lower limbs (6, 19–21). Understanding these biomechanical features is important for developing personalized rehabilitation strategies for AIS. However, the biomechanical changes of AIS patients are still controversial (22–24). The impact of TCMMT on biomechanics also has not been fully elucidated, and the quality of relevant studies still needs improvement (25, 26).

Thermography is a useful and noninvasive method of assessing muscular tension imbalance in the course of scoliosis (27). Combining with the plantar pressure, 3D gait analysis, and surface electromyography (sEMG) enables a comprehensive evaluation of the spine-limb biomechanical patterns during standing and walking in patients. Consequently, this study will employ the Cobb angle, the gold standard for scoliosis assessment (28), and integrate plantar pressure measurements, 3D gait analysis, surface electromyography (sEMG) and infrared thermography (IRT) to evaluate biomechanical changes. The study aims to elucidate the characteristics of biomechanical changes in AIS during standing and walking by comparing with healthy individuals at baseline, and provide evidence-based support for the efficacy and safety of combined TCMMT and Schroth method therapy by comparing baseline and post-treatment data of AIS.

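### The stated chi-square test at p<0.05 with 30 patients per arm cannot support the safety aim; adverse events need per-arm rates and a risk difference with confidence intervals

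*Protocol article*

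**What the plan says.** All references are to the protocol article.

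- **Aim (section 1, Introduction).** The trial is to "provide evidence-based support for the efficacy and safety of combined TCMMT and Schroth method therapy by comparing baseline and post-treatment data of AIS". The abstract's objective mentions efficacy and mechanisms but not safety.
- **Adverse events (section 2.4.2.4).** These stand among the secondary outcome measures. Any new symptom during treatment counts, and each event is recorded with its severity, timing, management and outcome. No expected rate, margin or safety hypothesis is given.
- **Analysis (section 2.5.2).** There are two general rules for categorical data. One is descriptive: "Categorical variables will be presented as frequencies or percentages". The other is a test: "For categorical variables, chi-square (χ^2^) tests will be performed". The threshold is "A *p*-value of <0.05 will be considered statistically significant". Adverse events are not named in either rule. The analysis set is everyone randomised who had at least one session.
- **Sample size (section 2.2.6).** Using Cobb angle means and standard deviations only, "it is determined that 30 patients need to be recruited for each group".

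**The concern.** Whether a patient had an adverse event is a categorical outcome, so the chi-square rule applies to it unless something else is specified. That test asks whether the data show a difference. It can reveal harm if the excess is large enough, but failing to reject says little when power is low. The safety aim, this test and a sample size fixed on another endpoint therefore do not fit together: the one result that would look favourable to safety is also a common result when there is real harm.

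The added treatment includes spinal manipulation in children aged 8 to 15, and the article expects its findings to inform clinical decisions. A non-significant comparison could then carry more weight than the data justify. The chi-square approximation is also at its weakest with few events, which is where uncommon harms would fall.

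**Working it through.** **1. The plan's own figure.** Inputs from section 2.2.6: means 10.87 and 14.97, SDs 3.60 and 5.01, two-sided alpha 0.05, power 0.90, attrition 15%.

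- Difference: 14.97 − 10.87 = 4.10.
- SD: √[(3.60² + 5.01²)/2] = 4.362.
- A two-sample t-test (noncentral t) needs 25 per arm (power 0.902). 25/0.85 = 29.4, so 30. The stated figure is reproduced, and it depends on the Cobb angle only.

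**2. Power for an excess of adverse events.** The document gives no event rates, so the rates below are assumptions. With X and Y as the numbers of affected patients in the experimental group (EG) and the control group (CG), X ~ Bin(30, p1) and Y ~ Bin(30, p0). Power is the sum of P(X=i)·P(Y=j) over all pairs with i > j and two-sided p<0.05. The miss rate is 1 − power.

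| CG v EG | Excess (points) | Missed, Pearson chi-square | Missed, Fisher |
|---|---|---|---|
| 5% v 10% | 5 | 90% | 98% |
| 5% v 15% | 10 | 74% | 91% |
| 5% v 20% | 15 | 55% | 76% |
| 5% v 25% | 20 | 37% | 56% |
| 5% v 30% | 25 | 22% | 37% |
| 10% v 20% | 10 | 81% | 90% |
| 10% v 30% | 20 | 50% | 63% |
| 10% v 40% | 30 | 20% | 30% |

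For 80% power the test would need 141 per arm at 5% v 15%, 76 at 5% v 20%, 199 at 10% v 20% and 62 at 10% v 30%.

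**3. What reaches significance (Pearson, 30 per arm).** With 0 affected in the CG, the EG needs 4. With 1 in the CG, it needs 6 (p = 0.044; 5 v 1 gives p = 0.085).

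**4. What a non-significant result leaves open.** For 4/30 v 1/30, p = 0.16. The difference is 13.3% − 3.3% = 10 points, with a Newcombe 95% confidence interval of −5.6 to +26.6 points. The interval still allows a large excess.

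**5. No events at all.** For 0/30 the exact upper limit is 1 − 0.05^(1/30) = 9.5% (one-sided 95%) or 1 − 0.025^(1/30) = 11.6% (two-sided 95%).

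**6. Sparse cells.** With equal arms, the expected number affected per arm is half the total. It is below 5 whenever fewer than 10 patients in all have the event.

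**The case against.** The strongest reply is that the defect lies in a possible future interpretation and not in the plan's text.

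- **No link to adverse events is spelled out.** Section 2.5.2 does not name adverse events, and the chi-square rule may be meant for sex and Risser grade, which section 2.4 lists as general information. This stands in part. Those are baseline characteristics, however. Adverse events are the one categorical outcome in section 2.4, and no other test is offered for them.
- **Chi-square is not the only rule for categorical data.** This stands: frequencies or percentages are also planned. Percentages without intervals do not show what the data can exclude.
- **No decision rule for safety exists.** This stands. A reader might infer that the trial will declare the treatment safe if p exceeds 0.05. The document does not say so, and that stronger charge should not be made.
- **All event rates are assumed.** This stands. Because any new symptom counts, rates for any event could be substantial, and very large excesses would probably be found (88% power for 5% v 35%, Pearson).
- **Detailed safety analysis may be in a document that is not shown.** This is fair for the choice of interval. It does not answer the mismatch, because no further detail can make a non-significant chi-square at this size support safety.
- **Sizing on the primary outcome is normal.** Agreed. The sizing is not the fault; it limits what may be claimed about harm.

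**Conclusion.** The concern holds as a mismatch between a stated aim and the only stated test. At 30 per arm, with assumed control rates of 5% or 10%, the Pearson test misses an excess of 5 to 20 points about 50% to 90% of the time. The exception in the table is 5% v 25%, missed 37% of the time. With Fisher's test the corresponding range is about 63% to 98%, and 56% for 5% v 25%. Power is about 80% by Pearson at 5% v 30% and 10% v 40%, so it would be wrong to say the trial is blind to all relevant harm.

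The conclusion rests on two things: that the categorical rule reaches adverse events, and that event rates lie in the assumed range. If adverse events were only to be tabulated, the power argument would fall away, but the aim of supporting safety would then have no stated inferential basis. The point deserves correction because a better method costs almost nothing. It does not affect the primary analysis.

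**What to change.** 1. In section 2.5.2, take adverse events out of the chi-square rule. Among all patients who received at least one session, report the number and percentage affected per arm with exact (Clopper-Pearson) 95% confidence intervals, and the EG − CG risk difference with a 95% confidence interval (for example Newcombe).
2. Add a sentence stating that a non-significant difference will not be taken as evidence of safety.
3. In the Introduction, limit the aim to describing safety, and tie any safety statement to the rates that the upper confidence limits exclude. For an event type not seen in 30 patients, that means rates above 9.5% (one-sided) or 11.6% (two-sided).

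The cost is a few sentences and one small table, with no new patients or data. The downside is a weaker safety claim.

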### Quality control

2.6

The study protocol has been approved by the Second Affiliated Hospital of Tianjin University of Traditional Chinese Medicine Ethics Committee. To ensure the quality of the research and the safety of participants, all researchers involved in the study will undergo unified and standardized training. TCMMT interventions will be performed by attending physicians with over 5 years of experience. Training and instructional videos will be recorded by senior chief physicians from the Department of Rehabilitation, and training and assessment protocols will be developed. Only researchers who pass the assessment will be qualified to perform the interventions. The study will establish a clear testing process and develop standardized operational procedures to strictly control the quality of the observed indicators and ensure the safety of participants. Participants will be enrolled strictly in accordance with the diagnostic, inclusion, and exclusion criteria. If a participant fails to complete the treatment and observation period as required by the protocol, researchers will attempt to contact them to inquire about the reasons and complete the assessment items. All data will be objectively collected using a combination of paper records and electronic documentation. All issues encountered during the trial will be accurately recorded. Outcome assessors and statisticians will be strictly blinded.

## Discussion

3

Scoliosis may lead to psychological issues, pain, respiratory complications, and functional limitations (37–40). Due to its complex three-dimensional spinal curvature and potential for progression, it poses a significant challenge in musculoskeletal rehabilitation (41). Therefore, early intervention during the adolescent developmental period is essential to prevent disease progression.

Numerous studies have demonstrated that Schroth exercise has positive effects on enhancing back muscle strength, improving respiratory function, slowing curve progression, reducing the Cobb angle, and lowering surgical rates (13, 42, 43). However, the efficacy of this method relies heavily on patients’ long-term compliance, and the postural correction training must be performed under correct biomechanical alignment conditions. TCMMT demonstrates notable advantages in this regard (16, 18). MT can enhance improvement in the Cobb angle, as well as alleviate pain, psychological distress, and disability. Furthermore, studies indicate that MT should be considered as a complementary and alternative therapy for the effective management of AIS patients (44, 45). However, the current evidence supporting MT for AIS remains insufficient, especially for TCMMT (18, 24, 46). This gap stems from both the unclear mechanisms underlying its therapeutic benefits and the generally low methodological quality of existing research. Moreover, the biomechanical alteration mechanisms in AIS are still controversial, and there is a notable lack of multimodal quantitative analysis characterizing these biomechanical changes in AIS.

This study innovatively integrates plantar pressure measurement, 3D gait analysis, sEMG, and IRT to establish a multimodal quantitative assessment framework. This system comprehensively captures the biomechanical characteristics of AIS patients during both static standing and dynamic walking. The approach synergistically complements and validates findings across multiple dimensions, including postural support, movement patterns, muscle activation, and thermal asymmetry, thereby significantly enhancing the objectivity and accuracy of the observed metrics. This protocol will not only enable an in-depth exploration of the biomechanical mechanisms underlying postural and gait abnormalities in AIS patients but also provide a precise and individualized basis for evaluating the therapeutic effects of TCMMT. It will hold substantial value for clinical research and possess promising application prospects.

The study will be conducted in strict adherence to the protocol, and all researchers will receive unified, standardized training to ensure compliance with regulated trial procedures. Based on these rigorous methodological designs, we believe that the results of this trial will provide new evidence regarding the role of manual therapy in AIS and make a substantive contribution to the current evidence base for the physical therapy of scoliosis.

This trial shares similar limitations with previous studies. Due to the nature of the interventions, neither the physicians nor the patients could be blinded, which may introduce bias. However, the primary objective of this study is to evaluate the additive effect of TCMMT within the combined regimen, rather than to independently validate the effectiveness of exercise therapy. This study will focus on assessing the corrective effect of combining TCMMT with the Schroth method on biomechanical imbalance by integrating multiple quantitative and objective evaluation metrics.

